## Abstract

**Background:**

Over 700,000 people die by suicide annually, making it the fourth leading cause of death among those aged 15-29 years globally. Safety planning is recommended best practice when individuals at risk of suicide present to health services. A safety plan, developed in collaboration with a health care practitioner, details the steps to be taken in an emotional crisis. SafePlan, a safety planning mobile app, was designed to support young people experiencing suicidal thoughts and behaviors and to record their plan in a way that is accessible immediately and in situ.

**Objective:**

The aim of this study is to assess the feasibility and acceptability of the SafePlan mobile app for patients experiencing suicidal thoughts and behaviors and their clinicians within Irish community mental health services, examine the feasibility of study procedures for both patients and clinicians, and determine if the SafePlan condition yields superior outcomes when compared with the control condition.

**Methods:**

A total of 80 participants aged 16-35 years accessing Irish mental health services will be randomized (1:1) to receive the SafePlan app plus treatment as usual or treatment as usual plus a paper-based safety plan. The feasibility and acceptability of the SafePlan app and study procedures will be evaluated using both qualitative and quantitative methodologies. The primary outcomes are feasibility outcomes and include the acceptability of the app to participants and clinicians, the feasibility of delivery in this setting, recruitment, retention, and app use. The feasibility and acceptability of the following measures in a full randomized controlled trial will also be assessed: the Beck Scale for Suicide Ideation, Columbia Suicide Severity Rating Scale, Coping Self-Efficacy Scale, Interpersonal Needs Questionnaire, and Client Service Receipt Inventory. A repeated measures design with outcome data collected at baseline, post intervention (8 weeks), and at 6-month follow-up will be used to compare changes in suicidal ideation for the intervention condition relative to the waitlist control condition. A cost-outcome description will also be undertaken. Thematic analyses will be used to analyze the qualitative data gathered through semistructured interviews with patients and clinicians.

**Results:**

As of January 2023, funding and ethics approval have been acquired, and clinician champions across mental health service sites have been established. Data collection is expected to commence by April 2023. The submission of completed manuscript is expected by April 2025.

**Conclusions:**

The framework for Decision-making after Pilot and feasibility Trials will inform the decision to progress to a full trial. The results will inform patients, researchers, clinicians, and health services of the feasibility and acceptability of the SafePlan app in community mental health services. The findings will have implications for further research and policy regarding the broader integration of safety planning apps.

**Trial Registration:**

OSF Registries osf.io/3y54m; https://osf.io/3y54m

**International Registered Report Identifier (IRRID):**

PRR1-10.2196/44205

## Introduction

### Background

More than 700,000 people die by suicide every year, representing the fourth leading cause of death among 15-29-year-olds globally in 2019 [1]. In Ireland, provisional figures indicate that 340 individuals died by suicide in 2020 [2]. Approximately one-third of people who die by suicide have been in contact with mental health services in the year before their death, and approximately 1 in 5 had contact with a health professional in the month before their death [3]. Suicide prevention guidelines recommend safety planning interventions alongside follow-up treatment by mental health services for those presenting to health services at risk of suicide [4]. However, the decision to implement safety planning in practice can be influenced more by clinicians’ beliefs about their efficacy than by empirical research [5]. The transient nature of suicidal ideation [6] may challenge the feasibility of paper-based plans and suggests the need for alternative modalities.

### Suicide Risk Factors

Suicidal behavior remains extremely difficult even for experienced clinicians to predict [7], leading researchers to focus their efforts on brief interventions designed for those at immediate risk [8]. A meta-analysis of 50 years of research in the area indicated that our predictive ability has not improved in that time and called for a shift from a focus on risk factors to machine learning–based risk algorithms [9]. The application of machine learning to large data sets may offer a means of better understanding the complex processes proposed by prominent theorists in the area [10,11]. Reflective of these research findings, recent clinical best practice guidelines recommend against the use of suicide risk assessment measures to predict future suicide or repeated self-harm in young people [12] and point to the importance of comprehensive psychosocial assessment and the development of a collaboratively developed and accessible safety plan.

### Safety Planning Intervention

The safety planning intervention (SPI) developed by Stanley and Brown [13] is a collaborative safety plan developed with a trained practitioner and recorded using a paper-based document. It is a brief structured intervention widely used in health systems and is often cited as the best practice in the treatment of patients with a high risk of suicide [14]. SPI is a key component across multiple treatment approaches targeting suicidal behavior, such as collaborative assessment and management of suicidality and cognitive behavioral therapy for suicide prevention. A safety plan outlines the steps to take in an emotional crisis and includes the identification of personalized warning signs, internal coping skills, people and places that provide distraction, people to contact for support, and contact details to use in a crisis. A cohort comparison trial of patients in the emergency department in US veteran hospitals presenting with suicidality found that SPI and phone follow-up significantly reduced suicidal behaviors and increased treatment engagement [13]. A recent systematic review of the effectiveness of SPI for adults experiencing suicide-related distress indicated improvements in suicidality (ideation, behaviors, and death), suicide-related outcomes (depression and hopelessness), and treatment outcomes (hospitalization) [15].

### Safety Planning Mobile Apps

Recording a safety plan on a mobile app may further enhance accessibility. The use of mobile devices by individuals at risk of suicide has been recommended by the World Health Organization [16]. The delivery of suicide prevention interventions through mobile health (mHealth) apps provides many opportunities when individuals need help the most [17]. SPI has been shown to be adaptable in its modality (digital or paper based) [15]. Further research is needed to better understand the extent to which using apps as an add-on to the treatment of patients with suicidal tendencies is feasible for clinicians and patients themselves. The MYPLAN safety planning app is undergoing clinical trial (ClinicalTrial.gov NCT02877316), and the Continuous Assessment for Suicide Prevention And Research study aims to implement a Dutch translation of the MYPLAN app alongside a self-monitoring app for suicidal patients in the Netherlands [18]. Researchers recently reported on the feasibility of using smartphone apps as treatment components for outpatients with depression and suicidal tendencies and found that mobile safety planning (using the BackUp app) was acceptable and usable for this group; however, the integration of apps into routine treatment needs to be further explored [19]. Indeed, researchers attest that effective interventions for suicidality do exist, but many patients do not receive them because implementation efforts tend to be time limited and unsystematic [20].

### Integrating mHealth in Mental Health Services

This protocol is underpinned by the research team’s previous research on the experiences of mental health professionals involved in integrating mHealth technology into existing mental health services [21]. The potential benefits of using mobile apps identified by mental health professionals include increased accessibility, increased engagement with young people, and the convenience and feasibility of a client using a mobile app during a crisis [21]. Many of the benefits identified in previous research are consistent with those asserted by mental health professionals in previous research [22]. A concern identified by professionals included the potential for the technology to be used instead of face-to-face services. Such findings are in line with previous research [23], suggesting that although professionals acknowledge their possible benefits and cost-effectiveness, health care providers are conservative about integrating mHealth technologies into everyday practice.

Mental health professionals identified the following barriers to adoption: lack of trust in the technology (privacy and confidentiality) and in the health care organization, training needs, policy guidance requirements, technical support requirements, and the need for further research. This mirrors the systematic review findings of the app literature, calling for further research before such technology is recommended or prescribed [24]. The benefits identified included the needs addressed by this technology to increase accessibility, enhance engagement, enhance the efficacy and generalization of skills acquired outside of the clinic setting, and the potential for individualized data collection to enhance treatment [24]. Similar enablers have been cited by mental health professionals in previous research [23].

### Engaging Young People

The use of mobile apps to record and store one’s safety plan may be particularly useful in supporting young people experiencing suicidal thoughts and behaviors, often simultaneously experiencing a transition to adulthood and to adult-focused services. The onset of many psychopathologies has been shown to coincide with the transition age [25,26]. Approximately 75% of all psychiatric disorders in adults start before the age of 24 years, and 50% of all psychiatric disorders start before the age of 14 years. However, there is discord in the pattern of increased risk of psychopathology in young people and mental health service use. Clinicians have previously identified the potential benefits of mobile app use in promoting engagement among young people with mental health services [21]. Approximately 64% of adolescents reported using apps to manage their mental health symptoms [27]. Indeed, 59% of health and fitness app users are aged between 18 and 34 years, indicating a higher level of engagement in health apps within this age group [28].

### Methodological Considerations

This trial is informed by a systematic review examining the effectiveness of mHealth technology tools in reducing suicide-specific outcomes, along with the review protocol [29,30]. This systematic review identified 7 studies that met the inclusion criteria. A total of 4 published articles that reported on the effectiveness of the following mobile phone apps were included: iBobbly [31], Virtual Hope Box [32], BlueIce [33], and Therapeutic Evaluative Conditioning [34]. The results demonstrated some positive impacts for individuals at an elevated risk of suicide or nonsuicidal self-injurious behaviors, including reductions in depression, psychological distress, and self-harm and increases in coping self-efficacy. However, none of the evaluated apps demonstrated the ability to significantly decrease suicidal ideation when compared with a control condition.

A significant limitation identified across all studies pertained to the heterogeneity of outcomes. Studies focused on differing suicide outcomes such as suicidal ideation as opposed to suicidal behaviors and often used differing outcome measures (ie, Beck Suicidal Intent Scale, Columbia Suicide Severity Rating Scale [C-SSRS], and Suicidal Ideation Attributes Scale). This hampered the extent to which the data could be compared and generalized. Another methodological issue is the practice of excluding individuals experiencing current suicidal thoughts or behaviors from participation. Importing empirically supported treatments for depression may not be appropriate because the trials in which efficacy was established excluded individuals who engage in suicidal behavior By embedding the trial within secondary-level mental health services, individuals at risk of suicide can participate safely while accessing mental health treatment. This methodological change is designed to reduce sample bias, enhance generalizability, and inform implementation research [20]. The evidence available indicates that suicide prevention mobile apps lead to reductions in depression, psychological distress, and self-harm in those at elevated risk of suicide or self-harm [29]. However, the pace of suicide prevention app development needs to be matched by scientifically rigorous research and the use of clinically valid methodologies that inform broader implementation of existing mental health services.

### SafePlan

SafePlan is a safety planning mobile app designed to be used as an adjunct to therapy for individuals experiencing suicidal thoughts and behaviors who access mental health services. The SafePlan app was designed and developed following significant stakeholder engagement and cocreation with young people, clinicians, suicide prevention researchers, suicide prevention policy developers, computer scientists, and human-computer interaction specialists. The SafePlan design process is described in detail elsewhere [35]. In addition to the capacity to develop and record a collaborative safety plan on the app, it also supports the completion of dialectical behavior therapy (DBT) diary cards, which was deemed appropriate. This feature was included on the advice of clinicians who noted that individuals who complete a safety plan as part of their treatment may also engage in DBT. The integration of DBT diary cards [36] can be enabled in the app’s clinical settings, in consultation with a mental health care professional, for patients who are engaged in this form of intervention. Consistent with research evaluating the Virtual Hopebox [32], the app also supports the inclusion and display of personalized Reasons for Living, such as photos, text, and videos, in visibly prominent places within the app.

This study details the first feasibility trial of the SafePlan mobile app within mental health services. Current Medical Research Council (MRC) guidance on complex interventions [37] advocates pilot trials and feasibility studies as part of a phased approach to the development, testing, and evaluation of health care interventions.

### Study Objectives

The study objectives are as follows: (1) examine the feasibility and acceptability of the SafePlan app as an adjunct to therapy for patients (aged 16-35 years) accessing secondary-level Irish mental health services and their clinicians; (2) assess the feasibility of the study procedures for both clinicians and patients within secondary-level mental health services; (3) determine the sample size required for a full randomized controlled trial (RCT) by collecting suicide outcome data at baseline, post intervention, and at 6-month follow-up; (4) determine whether the SafePlan app condition yields superior outcomes on the outcomes of suicidal ideation, suicidal behavior, and nonsuicidal self-injurious behavior at 6-month follow-up and post treatment when compared with the control condition; and (5) complete an economic analysis of the intervention.

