### Research Question

Is the SafePlan app, along with the proposed outcome measures, feasible and acceptable to patients aged 16-35 years at risk of suicide and their clinicians, in secondary-level mental health services in Ireland?

The feasibility and acceptability of using the following outcome measures in a full RCT will be assessed: the Beck Scale for Suicide Ideation (BSSI), C-SSRS, Coping Self-Efficacy Scale (CSES), Interpersonal Needs Questionnaire (INQ), and Client Service Receipt Inventory (CSRI) [38-42].

Data will be collected at baseline, post intervention, and at 6-month follow-up to determine whether the SafePlan app yielded superior outcomes on primary outcomes of suicidal ideation, suicidal behavior, and nonsuicidal self-injurious behavior when compared with the control group.

Participants: A total of 80 patients aged 16-35 years accessing secondary-level mental health services who present with current suicidal ideation, nonsuicidal self-injurious behavior, or a previous suicide attempt will be randomized to the SafePlan or control condition.Intervention: SafePlan is a safety planning mobile app informed by the paper-based SPI by Brown and Stanley [13]. Participants in the SafePlan condition will use the SafePlan app to record their safety plan in consultation with their mental health professional over an 8-week period as an adjunct to usual treatment.Comparison: The control group will receive treatment as usual (TAU) supplemented with the paper-based safety plan by Brown and Stanley [13] completed with their mental health professional.Outcome: The primary outcomes are feasibility outcomes and include the acceptability of the app to participants and clinicians, feasibility of delivery in this setting, recruitment, retention, and app use. Data collected on measures of suicidal ideation; suicidal behavior; and nonsuicidal self-injurious behavior at baseline, post intervention (8 weeks), and at 6-month follow-up will be used to compare changes in outcomes for the SafePlan condition relative to the control condition. A cost-outcome description will also be undertaken. Thematic analyses will be used to analyze the qualitative data gathered through semistructured interviews with patients and clinicians.

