### Sample Size

There is no established gold standard for calculating the sample size for a feasibility study, as the purpose of the study determines the sample size justification. In a systematic assessment of sample sizes in pilot and feasibility trials, Billingham et al [43] reported a median sample size of 36 participants, ranging from 10 to 300 participants. The aim of the SafePlan trial is to evaluate the feasibility of using the app as an adjunct to treatment. According to the clinician’s and service manager’s advice, a sample of 60 patients would be eligible for recruitment. With an expected 25% (20/80) dropout rate [43], a sample of 80 patients appeared adequate for the purposes of this study. Therefore, we will aim to recruit 80 patients from mental health services in Health Service Executive (HSE) West and Mid-West.

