## Discussion

### Principal Findings

This study will provide clinically valid data on the feasibility and acceptability of the SafePlan app as an adjunct to therapy for patients (aged 16-35 years) accessing community mental health services and their clinicians. It is hypothesized that patients and clinicians will find the app both feasible and acceptable and that important barriers and enablers to its use within Irish community mental health services will be identified. Data regarding the feasibility of the study procedures for both patients and clinicians will inform the decision to progress to a full trial. This is the first study to examine the feasibility of the SafePlan app and accompanying trial study procedures. Suicide outcome data collected at baseline, post intervention, and at 6-month follow-up will inform the sample size required for a full RCT. These data will also help determine whether the SafePlan app condition yields superior outcomes on standardized measures of suicidal ideation, suicidal behavior, and nonsuicidal self-injurious behavior at 6-month follow-up and post treatment when compared with the control condition. It is hypothesized that the SafePlan app condition will yield superior outcomes when compared with the control condition.

Safety planning interventions offer an evidence-based means of addressing suicidality in at-risk individuals [14]. A meta-analysis of safety planning–type interventions (SPTIs) for suicide prevention found that the relative risk of suicidal behavior among patients who received an SPTI compared with a control condition was 0.570 (95% CI 0.408-0.795; *P*=.001; number needed to treat: 55). The results support the use of SPTIs to help prevent suicidal behavior and the inclusion of SPTIs in clinical guidelines for suicide prevention [14]. SafePlan moves beyond the recording of safety plans using paper-based templates to record and store the plan, developed with a health care professional, on a mobile app. The results of this study will inform further research and the integration of safety planning apps within mental health services.

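### The protocol names two different sets of primary outcomes and promises to determine superiority, which neither the sample size nor the stated analysis supports

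*Protocol article*

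**What the plan says.** **Which outcomes are primary.** The Research Question section says data will be collected to find out whether the app gives "superior outcomes on primary outcomes of suicidal ideation, suicidal behavior, and nonsuicidal self-injurious behavior". Further down, under Outcome, the same section says "The primary outcomes are feasibility outcomes", listing acceptability, delivery, recruitment, retention and app use. The Methods paragraph of the Abstract agrees with the second statement.

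**What is promised.** Objective 4 under Study Objectives is to "determine whether the SafePlan app condition yields superior outcomes on the outcomes of suicidal ideation, suicidal behavior, and nonsuicidal self-injurious behavior" at 6 months and post treatment. The Abstract's Objective and the Research Question section also use the verb determine. The Discussion (Principal Findings) is a little softer, saying the data will help to determine superiority, but adds: "It is hypothesized that the SafePlan app condition will yield superior outcomes when compared with the control condition".

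**What sets the sample size.** The Sample Size section states that "The aim of the SafePlan trial is to evaluate the feasibility of using the app as an adjunct to treatment". It starts from 60 patients on service advice and continues: "With an expected 25% (20/80) dropout rate [43], a sample of 80 patients appeared adequate for the purposes of this study". It gives no alpha, power, target difference or SD.

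**What is analysed.** The Quantitative Data Analysis section specifies a between-group comparison of BSSI from baseline to 8 weeks, then within-group changes to explore preliminary efficacy. The 6-month data enter a repeated measures ANOVA run within each condition separately. The Columbia Suicide Severity Rating Scale (C-SSRS) is listed among the measures to be summarized.

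**The concern.** Which outcomes are primary decides how a trial is judged, and it should be settled before results are seen. As written, a later report could present either the feasibility outcomes or the three suicide outcomes as primary and cite the protocol for each.

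The superiority wording adds to this. The comparison is app against paper, with a safety plan in both arms, and the size was not chosen to separate them. A null result could be read as showing that the app is no better than paper when the trial had little chance of showing otherwise. A chance positive could be reported as a primary efficacy finding. In patients at risk of suicide, either misreading could influence whether services take up the app.

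Objective 4 and the analysis section also disagree about what will be compared between the arms, and when.

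**Working it through.** **1. The plan's own figure.** Taking 60 as the number wanted after dropout, 60 / (1 − 0.25) = 80. The stated total reproduces. With 1:1 allocation this is 40 randomized and 30 retained per arm. No power calculation is stated, so there is none to reproduce.

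**2. Objective 4 against the stated analysis.**

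| Objective 4 asks for a between-arm result on | Post treatment (8 weeks) | 6 months |
|---|---|---|
| Suicidal ideation (BSSI) | compared between groups | within each arm only |
| Suicidal behavior | no comparison named; C-SSRS summarized | no comparison named; C-SSRS summarized |
| Nonsuicidal self-injury | no comparison named | no comparison named |

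One of the six cells has a stated between-group comparison.

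**3. Suicidal ideation.** Inputs: 30 or 40 per arm (Sample Size section). Assumptions, since the protocol gives none: two-sided 5% two-sample t-test, effects in SD units, no baseline adjustment.

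- Detectable difference at 80% power. Normal approximation: (1.960 + 0.842) × √(2/n), which is 0.72 SD for n = 30 and 0.63 SD for n = 40. Exact t calculation: 0.74 and 0.63 SD.
- Half-width of the 95% confidence interval, t × √(2/n): 0.52 SD (n = 30) and 0.45 SD (n = 40).

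| Assumed true difference | Power, 30 per arm | Power, 40 per arm |
|---|---|---|
| 0.2 SD | 12% | 14% |
| 0.3 SD | 21% | 26% |
| 0.5 SD | 48% | 60% |

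With baseline adjustment the residual SD shrinks by √(1 − r²). For an assumed r of 0.5 to 0.7 (normal approximation), power at 0.3 SD is 27–37% with 30 per arm and 34–47% with 40. At 0.5 SD it is 61–77% and 73–88%.

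**4. Suicidal behavior.** The Discussion cites a relative risk of 0.570 and a number needed to treat of 55 for safety planning against control. These imply a control risk of 1 / (55 × (1 − 0.57)) = 4.23% and a treated risk of 0.57 × 4.23% = 2.41%. With 40 per arm the expected events are 40 × 0.0423 = 1.7 and 40 × 0.0241 = 1.0.

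The figures come from a different contrast, and this population's risk may be higher, so the control risk is varied with the relative risk held at 0.57:

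| Control risk | Power, 30 / 40 per arm (normal approximation) | Power, 30 / 40 per arm (Fisher exact) |
|---|---|---|
| 4.2% (derived) | 6% / 7% | 0.1% / 0.3% |
| 10% (assumed) | 9% / 11% | 2% / 3% |
| 20% (assumed) | 15% / 18% | 7% / 12% |
| 30% (assumed) | 21% / 27% | 14% / 20% |
| 50% (assumed) | 40% / 50% | 30% / 42% |

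No cell comes near 80%. For nonsuicidal self-injury the protocol gives neither an event rate nor an effect, so nothing is computed.

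**The case against.** The strongest reply is that the context already limits the claim. The study is called a pilot, feasibility is named as primary in the Abstract and under Outcome, and progression rests on a framework about recruitment, retention, adherence and acceptability. The Outcome Measure Feasibility section calls BSSI the proposed primary outcome for a full trial, so the other use of primary may be a slip for that future trial. This is plausible, but it does not remove the conflict: the BSSI remark covers one measure, while the Research Question section names three outcomes and ties them to this trial's data.

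It is also fair that the ideation effects above are assumptions and that adjustment helps. Under the most favourable case shown (40 per arm, r = 0.7), a 0.5 SD difference has 88% power. A reader might infer that superiority cannot be shown at all; the documents do not support that. A large difference could be detected, and a moderate one under favourable assumptions.

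A reader might equally take the near-zero power for suicidal behavior as the protocol's own figure. It is not. The 4.2% risk is derived from safety planning against control, whereas here both arms have a safety plan, and the sub-1% value also depends on choosing Fisher's exact test, which the protocol does not name. The same point suggests that 0.57 is optimistic for this comparison. Nor should one assume that the true difference must be small: the app also holds personal media and optional diary cards, and the background reports reductions in self-harm with other apps, although none significantly reduced ideation against control.

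Two further inferences are unsupported. Objective 4 might suggest six significance tests with inflated false-positive risk, but the analysis section does not plan six tests. And the protocol says BSSI data will be used to size the full trial, but nowhere that the observed difference will be the target.

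**Conclusion.** The point holds in this form. The Research Question section contradicts itself on the primary outcomes, and the promise to determine superiority on three outcomes at two times goes beyond both the sample size and the stated analysis. The contradiction and the gap between objective 4 and the analysis section rest on the text alone.

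The power part rests on a two-sided 5% test and assumed effects. Without adjustment, differences below about 0.63 to 0.74 SD in ideation fall short of 80% power. With adjustment, a 0.3 SD difference still has less than 50%. For suicidal behavior at a relative risk of 0.57, power is at or below about 50% for control risks from 4% to 50%. The trial can estimate a BSSI difference with a stated, wide interval. It should not claim to settle superiority.

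**What to change.** 1. In the Research Question section, remove the label primary from the three suicide outcomes, so that feasibility outcomes are the only primary outcomes.
2. Reword objective 4, and the matching text in the Abstract's Objective, the Research Question section and the Discussion, along these lines: the between-arm difference in BSSI will be estimated with a 95% confidence interval at 8 weeks and 6 months as an exploratory analysis; suicidal behavior and nonsuicidal self-injury will be described by arm; no conclusion about superiority will be drawn.
3. In the Quantitative Data Analysis section, add the between-arm BSSI estimate at 6 months, so that the analysis matches the reworded objective.

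The directional hypothesis in the Discussion can stay as the idea behind a full trial, provided the text says this pilot does not test it.

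The cost is a more modest claim, a wording change and one extra estimate from data already being collected. No further patients or measurements are needed.
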